#### Sample size

In the practices in the practice accreditation program up to 2006 (n = 139), the following median values at practice level were found on indicators referring to patients with CVD: 53% for acceptable blood pressure levels; 36% for acceptable cholesterol levels; and 38% for use of anticoagulents (unpublished data at IQ healthcare, 2005 and 2006). These data suggest that the current scores on the primary outcomes are in the range of 35% to 55%, which imply that substantial improvement is possible in many practices. The proposed study has been powered to detect a difference of 10% (from 55% to 65%), not yet taking control for baseline values into account because of uncertainty regarding the correlation between baseline and follow-up measures.

We expected that the accreditation and improvement program will have an effect of 5% to 10% absolute change, which is the median value of effect sizes in a comprehensive review of 235 studies on quality improvement [14]. Other assumptions were a power = 0.80, alpha = 0.05, and ICC = 0.05. Given the sample of 30 patients per practice per indicator, we aimed to include 31 practices in each group. Allowing for dropout, we aim to include 35 practices in each group (n = 70 practices in total). This number is feasible, given the recruitment rate for the accreditation in 2006.

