**Methods/design:**

We have planned a two-arm cluster randomized trial with a block design. Seventy primary care practices will be recruited from those who volunteer to participate in the practice accreditation program. Primary care practices will be the unit of randomization. A computer list of random numbers will be generated by an independent statistician. The intervention group (n = 35 practices) will be instructed to focus improvement on cardiovascular risk management. The control group will be instructed to focus improvement on other domains in the first year of the program. Baseline and follow-up measurements at 12 months after receiving the accreditation certificate are based on a standardized version of the audit in the practice accreditation program. Primary outcomes include controlled blood pressure, serum cholesterol, and prescription of recommended preventive medication. Secondary outcomes are 15 process indicators and two outcome indicators of cardiovascular risk management, self-reported achievement of improvement goals and perceived unintended consequences. The intention to treat analysis is statistically powered to detect a difference of 10% on primary outcomes. The economic evaluation aims to determine the efficiency of the program and investigates the relationship between costs, performance indicators, and accreditation.

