#### Measures of effectiveness

The effect evaluation aims to determine the effectiveness of the program on primary performance indicators for CVRM and to determine the potential impact of the program on other indicators for CVRM, self-reported goal attainment in the intervention group, and unintended consequences.

Primary outcomes have been selected from the 20 quality indicators for established CVD [21], which were developed by DCGP (Table 1), and are:

1. The percentage of patients in the practice with known established CVD who have systolic blood pressure below 140 mmHg.

2. The percentage of patients in the practice with known established CVD who have LDL cholesterol below 2.5 mmol/l.

3. The percentage of patients in the practice with known established CVD with a record that aspirin, an alternative anti-platelet therapy, or an anticoagulant has been prescribed.

**Table 1 T1:** Indicators for cardiovascular risk management

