#### Statistical methods

The study groups will be compared at baseline regarding known determinants of cardiovascular care and its improvement. These include patient factors [27,28] (*e.g.*, age, multi-morbidity, ethnicity at practice level) and practice characteristics [22,29] (*e.g.*, availability of nurses, delegation of medical tasks to assistance, practice size). Only factors emerging from previous research are considered to avoid overcorrection in the primary analysis. A logistic regression model will be constructed for each outcome to analyze these outcomes in relation to group (intervention, control) and measurement moment (baseline, follow-up). Identified differences between the groups at baseline will be included in this analysis. Random coefficients will be included to allow for the clustering of data within practices. Each of the secondary outcomes (clinical and organizational indicators) will also be analyzed in this way. Finally, if an internally consistent scale can be constructed (reflected by high reliability coefficients of the combined score), we will develop an aggregated measure of outcome, and use this in a similar random coefficients linear regression analysis.

To identify the effectiveness of this program on attainment of practice-defined goals and its perceived unintended consequences, the second key objective, a descriptive analysis will be performed aimed at determining what proportion of self-defined goals for improvement was achieved by the practices and straightforward listing of the GP views on unintended consequences of the practice accreditation program.

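### Three unranked primary outcomes share one sample-size calculation at alpha 0.05, so the stated 0.05 and 0.80 hold per outcome only and no rule links them to an overall claim of effectiveness.

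*Protocol article*

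**What the plan says.** Under Measures of effectiveness, "Primary outcomes have been selected from the 20 quality indicators for established CVD". Three are listed: systolic pressure below 140 mmHg, LDL below 2.5 mmol/l, and a recorded antiplatelet or anticoagulant prescription. The abstract, the objectives and Table 1 treat the same three as primary, without an order.

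Under Statistical methods, "A logistic regression model will be constructed for each outcome to analyze these outcomes in relation to group" and measurement moment. The same section adds a conditional further measure: if the indicators form a reliable scale, "we will develop an aggregated measure of outcome, and use this in a similar random coefficients linear regression analysis". Its rank relative to the three primary outcomes is not given.

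Under Sample size, one scenario is used, 55% against 65%, with 30 patients per practice per indicator. "Other assumptions were a power = 0.80, alpha = 0.05, and ICC = 0.05". This gives 31 practices per group, raised to 35 for dropout. The abstract says: "The intention to treat analysis is statistically powered to detect a difference of 10% on primary outcomes".

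The article does not say whether one, two or all three outcomes must reach significance before the programme is called effective.

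**The concern.** The overall aim is to determine whether the accreditation programme is effective, and the Discussion expects stakeholders to base policy decisions on the results. With three primary outcomes, a reader needs to know what result would count as effectiveness and with what error and power. The stated figures answer this for one outcome at a time. They do not answer it for a claim that draws on all three, whichever usual rule is used: an any-one rule raises the error above 0.05, and an all-three rule lowers the power below 0.80. An aggregated score of undefined rank would add another route to a positive claim.

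**Working it through.** **Inputs.** From Sample size: 55% and 65%, alpha 0.05, power 0.80, ICC 0.05, 30 patients per practice, 31 and 35 practices per group. From Measures of effectiveness: three primary outcomes. Assumed: the correlation r between the three test statistics, taken as equal for each pair, since the protocol gives none.

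**1. The plan's own figure.** For two proportions, two-sided, pooled variance under the null, no continuity correction:

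n = [1.960 × √(2 × 0.60 × 0.40) + 0.842 × √(0.55 × 0.45 + 0.65 × 0.35)]² / 0.10² = 375.6, so 376 per group.

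Design effect = 1 + (30 − 1) × 0.05 = 2.45. Practices = 376 × 2.45 / 30 = 30.7, so **31**, as stated. A one-sided 0.05 would give 25. At 0.05/3 two-sided, n = 502 and 502 × 2.45 / 30 = 41.0, so 41. The plan therefore gives the full two-sided 0.05 to one outcome.

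**2. Error if any one outcome suffices.** Each outcome is taken as tested at two-sided 0.05. With independent tests the error is 1 − 0.95³ = 0.143. Correlated values come from numerical integration over equicorrelated normal statistics. Joint power for step 3 is shown in the same table.

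| r | At least one false positive, either direction | At least one in favour of the programme (nominal 2.5%) | Power that all three succeed, each at 0.80 |
|---|---|---|---|
| 0 | 14.3% | 7.3% | 0.51 |
| 0.5 | 12.5% | 6.3% | 0.61 |
| 0.8 | 9.8% | 4.9% | 0.69 |

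**3. If all three must succeed.** No alpha split is needed and the error is at most 5%. With independent tests joint power is 0.80³ = 0.51, rising with correlation as in the last column.

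**4. Power under Holm.** Holm compares the smallest p-value with 0.05/3 = 0.0167, the next with 0.025 and the largest with 0.05. The effective size per group is 31 × 30 / 2.45 = 379.6, or 35 × 30 / 2.45 = 428.6.

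- Power for one outcome at 0.0167 is 0.663 with 31 practices and 0.725 with 35 (pooled variance), or 0.667 and 0.729 (unpooled). At 0.05 it is 0.804 and 0.849 (pooled).
- Simulation with 31 practices and a 10-point gain on all three outcomes gives power for at least one Holm claim of 0.96 at r = 0, 0.88 at 0.5 and 0.80 at 0.8. Average power per outcome is 0.76, 0.74 and 0.73.

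**5. What baseline adjustment might return.** Assume 30 different patients per practice at each time and a cluster autocorrelation CAC. The correlation of practice means is CAC × (30 × 0.05) / 2.45 = 0.612 × CAC, and the variance is multiplied by 1 − (0.612 × CAC)².

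- CAC 0.5: correlation 0.306, factor 0.906, power at 0.0167 with 31 practices about 0.71.
- CAC 0.8: correlation 0.490, factor 0.760, power about 0.80.

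Neither CAC is in the protocol.

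**The case against.** The strongest reply is that the Sample size section states a per-outcome calculation, does it correctly, and never claims family-wise control. A success rule may sit in a full protocol or analysis plan that is not shown, and its absence from a condensed article would not be a finding by itself. The first objective also speaks of the primary indicators in the plural, and the Economic analysis plans a separate ratio for each outcome. This fits outcome-by-outcome reporting, for which 0.05 and 0.80 per outcome are the relevant figures and the need for adjustment is debated.

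Much of this stands. A reader might infer that the trial simply has a 12 to 14% false-positive rate. The document does not support that: no test level per outcome is written and no any-one rule is stated. The inflation is conditional on that reading, it counts errors in both directions, and it falls to 9.8% at correlation 0.8.

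A reader might also infer that 0.80 is not the power of any error-controlled claim. That is wrong, because the first outcome in a fixed sequence is tested at 0.05 and keeps 0.80. Nor is the cost of Holm only a loss: power for at least one claim stays at 0.80 or above in the scenarios in step 4.

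What the objection does not remove is that this document itself fixes three unranked primaries and a size based on the full 0.05 for one of them. A later Holm rule, or an all-three rule, would leave the published 0.80 too high for the claim it appears to support.

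**Conclusion.** The point holds in a conditional form. The stated 0.05 and 0.80 are correct for each outcome taken alone and do not carry over to a claim across the three. Under an any-one reading, the error in either direction is about 10 to 14% for correlations from 0 to 0.8, and the error favouring the programme is about 5 to 7% against 2.5%. Under an all-three reading, the error is controlled but joint power is about 0.5 to 0.7. These ranges rest on assumed equal correlations, two-sided 0.05 tests per outcome and the protocol's planning values. The design itself stands; the decision rule and the power statement should be corrected.

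**What to change.** State in the analysis section that the three primary p-values are tested with Holm's procedure at a family-wise two-sided 0.05, that effectiveness is claimed only for the outcomes that pass, and that any aggregated score lies outside the primary family. Holm is valid under any correlation. A fixed sequence or an all-three rule would also close the gap, but the first needs a ranking the protocol does not give and the second has the joint power shown above.

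In Sample size, say that 0.80 is power per outcome at unadjusted 0.05. Add the power at the strictest Holm step (about 0.66 with 31 practices per group, 0.73 with 35) and the power for at least one claim (about 0.80 to 0.96 with 31 practices if all three improve by 10 points). Qualify the abstract's power sentence in the same way.

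The cost is wording and a less favourable per-outcome figure. Restoring 0.80 at 0.0167 without baseline adjustment would take 41 practices per group, or about 47 with the same dropout allowance (41 × 35 / 31 = 46.3). Recovery through baseline adjustment should not be presented as assured, because the Sample size section itself calls the baseline to follow-up correlation uncertain. The Discussion reports that no data had been cleaned or analysed at submission, so at that point the rule could still be set without knowledge of the results.

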#### Time frame of the study

The study is planned from September 2008 until September 2012. In months 1 to 18, practices are recruited and included in the project and go through the accreditation procedure. The baseline data collection will take place in these months. During months 3 to 42, practices (in the intervention group) work on improving their management of CVD, practices in the control group on improvements in other areas. In months 18 to 42, follow-up measurements in intervention and control practices are planned. During months 43 to 48, data will be analyzed and reported.

## Discussion

The sample of participating primary care practices in this study is composed of volunteers for the practice accreditation program and therefore not nationally representative for primary care practices in the country. This reflects current practice, in which practice accreditation is a voluntary activity. It implies that study results cannot be generalized to the (currently hypothetical) situation of obligatory accreditation. Furthermore, we only collect data on CVRM; therefore, we cannot make statements about the effects of the program on other chronic illnesses.

Because both intervention and control groups start with accreditation, this project cannot pick up non-specific effects of the practice accreditation program. For example, we expect that practices prepare for accreditation by improving their practice (*e.g.*, involve a practice nurse). We intend to compare the groups with other, independent samples of practices that provide data on cardiovascular care to get an impression of the representativeness of our sample of practices.

With the results of this study, we hope to make a contribution with regard to further development and adjustment of the practice accreditation program. Previous research [32] has shown that the program is time-consuming for participating practices. Furthermore, it costs a considerable amount of money to participate in the program. It is important to gain more information about the effectiveness and efficiency of the program to assess if participation is worthwhile regarding the quality of CVRM. With these results, stakeholders can make policy and management decisions with regard to the use of the program.

No data cleaning or analysis has occurred prior to submission of the manuscript.

## Abbreviations

CVD: Cardiovascular disease; CVRM: Cardiovascular risk management; DCGP: Dutch College of General Practitioners; COPD: Chronic obstructive pulmonary disease; GP: General Practitioners; LDL-cholesterol: Low Density Lipoprotein-cholesterol; TIA: Transient Ischemic Attack; VIP: The Visit Instrument to asses Practice management (Visitatie Instrument Praktijkvoering); ICPC: International Classification of Primary Care; PACIC: Patient Assessment of Chronic Illness Care; TSRQ: Treatment Self-Regulation Questionnaire; ICER: Incremental cost effectiveness ratio; CEAC: Cost-effectiveness acceptability curve.
